## Abstract

**Background:**

Intravenous (IV) vasopressors to support hemodynamics are a primary indication for intensive care unit (ICU) admission. Utilization of oral vasopressor therapy may offer an alternative to IV vasopressor therapy in the ICU, thus decreasing the need for ICU admission. Oral vasopressors, such as midodrine, have been used for hemodynamic support in non-critically ill patients, but their evaluation in critically ill patients to potentially spare IV vasopressor therapy has been limited.

**Methods:**

The LIBERATE study will be a multicenter, parallel-group, blinded, randomized placebo-controlled trial. It will recruit adult (i.e., age ≥ 18 years) critically ill patients receiving stable or decreasing doses of IV vasopressors. Eligible patients will be randomized to receive either midodrine 10 mg administered enterally every 8 h or placebo until 24 h post-discontinuation of IV vasopressors. The primary outcome will be ICU length of stay. Secondary outcomes include all-cause mortality at 90 days, hospital length of stay, length of IV vasopressor support, re-initiation of IV vasopressors, rates of ICU readmission, and occurrence of AEs. Health economic outcomes including ICU, hospital and healthcare costs, and cost-effectiveness will be evaluated. Pre-planned subgroup analyses include age, sex, frailty, severity of illness, etiology of shock, and comorbid conditions.

**Discussion:**

LIBERATE will rigorously evaluate the effect of oral midodrine on duration of ICU stay and IV vasopressor support in critically ill patients.

**Trial registration:**

ClinicalTrials.gov NCT05058612. Registered on September 28, 2021

**Supplementary Information:**

The online version contains supplementary material available at 10.1186/s13063-022-06115-0.

## Introduction

### Hemodynamic support in the ICU

Resuscitation and hemodynamic support with intravenous (IV) vasopressors is a prime indication of treatment in intensive care unit (ICU) settings [1]. Hemodynamic support is typically provided with intravenous (IV) vasopressors, catecholamines, or vasopressin [2–4]. However, the intravenous administration of vasopressors is associated with a risk of significant adverse effects including tissue necrosis, tissue thrombosis, cardiac dysrhythmias, and dysfunction as well as bowel ischemia. Furthermore, the presence of central venous catheters required for the infusion of IV vasopressors can contribute to risk of central venous catheter-associated bloodstream infections, venous thrombosis, and limited mobility [5–8]. Oral vasopressors have been historically used for hemodynamic support in non-critically ill patients, but their utility in ICU settings requires further exploration. One such oral vasopressor is midodrine (midodrine hydrochloride), which is a peripherally acting alpha-agonist that has previously been used to attenuate symptoms of chronic orthostatic hypotension, for management of intradialytic hypotension, and for treatment of hepatorenal syndrome [9–11].

### Hemodynamic support with midodrine

Previous studies have evaluated the use of midodrine for vasopressor support in the ICU (Table 1) [12–16]. The first of these studies by Levine et al. was a single-center, prospective cohort study of 20 patients which evaluated the effect of concurrent administration of midodrine on vasopressor requirements. The authors found that by using midodrine it was possible to decrease the administration rate of IV phenylephrine required for hemodynamic support [13]. Following these results, Poverno et al. evaluated the use of midodrine in 188 patients in a single-center retrospective cohort study, where the primary outcome was the duration of IV vasopressor therapy [14]. Importantly, in patients receiving midodrine, there was a significant reduction in vasopressor duration by 1.2 days. There was no change in ICU or hospital lengths of stay (LoS), nor in rates of ICU readmissions. In the recently published MIDAS study, a multicenter study conducted by Santer et al., 136 patients received oral midodrine or placebo in addition to their standard IV vasopressor therapy [15]. Study results did not find a difference in the time to vasopressor discontinuation between study groups. However, this trial was small, limited to mostly surgical patients, and was performed over 7 years. As such, the MIDAS study may have limited generalizability and may be impacted by temporal changes in critical care practice (i.e., changing co-interventions, evolving standard of care). In a larger single-center retrospective study, Whitson et al. evaluated 275 septic patients and found that midodrine use decreased IV vasopressor duration by 0.9 days (*p* < 0.001) and decreased ICU LoS by 2 days (9.4 vs. 7.5 days, *p* = 0.017) [16]. The LIBERATE study will evaluate the expanded role of midodrine for any hypotensive patient in the ICU.

**Table 1 Tab1:** Previous trials evaluating the role of midodrine for hypotension

Author	Year	Patients	Population	Study type	Outcomes	Results
Levine et al.	2013	20	Surgical	Single-center prospective cohort	• **Dose of IV vasopressor**	• Decrease of −1.58 mcg/min of phenylephrine with use of midodrine
Poverno et al.	2016	188	General	Single-center retrospective cohort	• **Duration of IV vasopressor** • ICU LoS • Hospital LoS • ICU readmission	• Midodrine patients required IV vasopressors for 1.2 days following initiation of midodrine • No change in ICU length of stay • Increased hospital length of stay with midodrine (12.0 vs. 9.5days) • No difference in ICU readmission between groups
Whitson et al.	2016	275	Medical	Single-center retrospective cohort	• **Duration of IV vasopressor** • ICU LoS • Hospital LoS • IV vasopressor reinstitution • Mortality	• Decrease duration of IV vasopressors by 0.9 days • Decrease ICU length of stay (7.5 days vs. 9.4 days) with midodrine • Decrease hospital length of stay (21.9 days vs. 24.2 days) with midodrine • No mortality difference between groups
Santer et al.	2020	136	General	Multicenter RCT	• **Duration of IV vasopressor** • ICU LoS • Hospital LoS • ICU readmission • Adverse events	• No difference in duration of IV vasopressors • No difference in ICU or hospital LoS • No difference in ICU readmissions between groups

### Rationale for the study

LIBERATE hypothesizes that oral midodrine will lead to earlier liberation from IV vasopressor support in critically ill patients with refractory hypotension. Currently, literature evaluating the effects of oral midodrine on weaning from IV vasopressor support is unclear and conflicting, and the trials conducted to date have been underpowered to detect clinically important differences in patient-centered and health service endpoints [12–16]. In the environment of strained healthcare resources, limited ICU capacity, and constant pressure on ICUs worldwide, the ability to safely wean patients from IV vasopressors with transition to oral hemodynamic supporting agents may improve how patients navigate through the healthcare system [12].

## Preparatory work

Previously, we have conducted an internal pilot randomized controlled trial (RCT) (NCT04489589) that obtained Health Canada approval and No Objection Letter (obtained April 3, 2020), confirming the feasibility of patient recruitment, implementation of the protocol, and patient follow-up (Additional file 1). The experiences learned while conducting the pilot RCT informed protocol modifications in the main phase of the study as reported herein. Allocation concealment and blinding was maintained throughout this pilot, and previously recruited patients will be included in this trial.

### Primary aim and objectives

To determine the efficacy of the use of an enteral peripheral vascular vasoactive agent (i.e., midodrine hydrochloride) to facilitate liberation from continuous infusion of IV vasopressor therapy in critically ill patients with refractory hypotension.

#### Primary objectives

To compare the effect of enteral midodrine vs. placebo in critically ill patients with refractory hypotension receiving continuous IV vasopressor therapy on ICU length of stay.

#### Secondary objectives

To evaluate the effect of enteral midodrine vs. placebo on additional patient-centered outcomes in critically ill patients with refractory hypotension receiving continuous IV vasopressor therapy.

#### Tertiary objectives

To determine the health economic effects of the usage of midodrine vs. placebo in critically ill patients with refractory hypotension receiving continuous IV vasopressor therapy. The health economic analysis plan and protocol will be published separately.

## Methods

### Study design

The LIBERATE trial is a multicenter, concealed-allocation parallel-group blinded placebo-controlled randomized trial. The trial will randomly allocate 350 critically ill adult patients receiving IV vasopressor therapy to either midodrine 10 mg or identical placebo. This dose was chosen based on the product monograph suggested dosing. The investigational product will be administered enterally every 8 h for the duration of their IV vasopressor therapy and up to 24 h after discontinuation of their IV vasopressor therapy. Table 2 shows a timeline of trial activities. The SPIRIT checklist is available in Additional file 2.

**Table 2 Tab2:** Trial activity timeline

Time points		Study period			
	Enrollment	Post-enrollment			
	Day 1	Days 2–30	ICU/hosp discharge	Month 6	Month 9
Enrolment					
Eligibility screen	x				
Informed consent	x				
Treatment allocation	x				
Intervention					
Midodrine or placebo	x				
Assessments					
Age, sex	x				
Weight and height	x				
Date of eligibility	x				
ICU and hospital admission date	x				
ICU admission type	x				
ICU admission diagnosis	x				
Clinical frailty scale score	x				
APACHE II score	x				
Etiology of shock	x				
Comorbid illness	x				
Vasopressor therapy	x	x			
Mechanical ventilation	x	x			
Total duration of vasopressor support			x		
Vasopressors initiated after cessation		x			
ICU or hospital death		x			
Date of ICU death or discharge		x			
ICU length of stay			x		
Hospital length of stay			x		
ICU readmission during hospital stay			x		
Discharge location from hospital			x		
Persistent organ dysfunction or death				x	x
EQ-5D					x
Adverse events	x	x	x	x	x
Cardiac events (clinically significant bradycardia, acute coronary syndrome)	x	x	x	x	x
Allergic events (paresthesia, piloerection, dysuria, pruritis, chills, pain, rash)	x	x	x	x	x
Hypertension	x	x	x	x	x
Bowel ischemia	x	x	x	x	x
Limb ischemia	x	x	x	x	x
Stroke	x	x	x	x	x
Protocol violations	x	x	x	x	x

### Study setting

The study will be centrally coordinated by the Research Office in the Department of Critical Care Medicine at the University of Alberta Hospital. The study will be performed at 7 mixed medical/surgical ICUs throughout Alberta. Additional sites outside of Alberta may be added, as necessary.

### Inclusion criteria

Adults age ≥ 18 years receiving IV vasopressor support (i.e., norepinephrine ≥0.05 mcg/kg/min, epinephrine ≥0.05 mcg/kg/min, vasopressin ≥0.04 U/min, or phenylephrine ≥0.1mcg/kg/min) and decreasing vasopressor dose(s) (i.e., current dose less than peak dose(s))

### Exclusion criteria

Greater than 24 h from peak vasopressor doseContraindication to enteral medications or known allergy to midodrinePrevious receipt of midodrine in last 7 daysExpected death or anticipated withdrawal of life-sustaining therapies in next 24 hPregnancy

### Rationale for eligibility criteria

The LIBERATE study is a real-world, pragmatic study for the effectiveness of utilizing midodrine, an enteral alpha-agonist, to facilitate the weaning of IV vasopressors for patients recovering from critical illness. Previously, the utility of midodrine has been studied predominantly in patients with septic shock [16]. However, as midodrine is an alpha-agonist, it can be utilized for any hypotensive condition [17]. As we are aiming to study midodrine for the facilitation of weaning of IV vasopressors, we wanted to ensure at least a stable or de-escalating dose of IV vasopressors prior to initiating enteral midodrine therapy. By excluding patients with peak doses of vasopressors > 24 h prior to randomization, we exclude a timing bias relating to the decision to initiate enteral midodrine therapy. We will be continuously assessing for maximal vasopressor dose (i.e., rolling 24-h peak vasopressor dose assessment) to ensure that any and all weaning events are identified and that we still only enroll within 24 h of peak dose.

### Recruitment strategy and approach for consent

All consecutive eligible patients will be invited to participate in the trial following referral by the treating ICU team. If the patient is unable to provide consent within the time window allowed by the protocol, his or her surrogate decision-maker (SDM) and/or legally authorized representative may be approached in person or, if necessary, contacted by telephone. The local research team could also enroll eligible patients and obtain consent subsequently as per local Research Ethics Board (REB) recommendations under a deferred consent model.

### Ethics

#### Health Canada Authorization

Since the proposed use of midodrine in the present study is outside the parameters of the Drug Identification Number (DIN) application, a Clinical Trial Application (CTA) has been submitted to Health Canada and a No Objection Letter (NOL) has been obtained (HC6-24-c236428, April 3, 2020).

#### Research ethics approval

This study was reviewed and approved by the University of Alberta Research Ethics Board (Pro00096716, August 8, 2020). All participating clinical sites will receive REB or Institutional Review Board (IRB) approval prior to commencing patient enrollment. Depending on local standards, centralized or local REBs/IRBs will approve the study protocol of each site. Before launching the trial, each clinical site will provide the coordinating center with a copy of its ethics approval letter.

#### Protocol amendments

Any modifications to the protocol which may impact the conduct of the study, potential benefit to the patient or may affect patient safety, including changes of study objectives, study design, patient population, sample sizes, study procedures, or significant administrative aspects, will require a formal amendment to the protocol. Such amendments will be reviewed and approved by the Steering Committee.

### Randomization

Randomization will be done as per a computer-generated randomization schedule through a Web-based portal (i.e., Randomize.net). Eligible patients will be randomized in a 1:1 ratio to midodrine or placebo using permuted blocks of undisclosed and variable size. We will stratify randomization by site.

Randomization will be conducted by the study pharmacists after receiving written notification of the patient enrollment from the study team. The study pharmacy will then prepare and dispense the appropriate blinded study treatment.

### Trial interventions

#### Experimental arm

Patients in the experimental arm will receive midodrine 10 mg, administered enterally, q8h from time of study inclusion to 24 h post-IV vasopressor support termination. This will be administered as a capsule containing the active substance.

#### Control arm

Patients in the control arm will receive a placebo, administered enterally, q8h from time of study inclusion to 24 h post-IV vasopressor support termination. This inactive substance will be administered as a capsule that appears identical to the midodrine capsule.

The administration of capsules will be the responsibility of the blinded bedside nurse. There is no maximum duration of study treatment.

### Rationale for interventions

#### Co-interventions

Other than the study intervention, co-interventions (i.e., steroids, IV fluids, additional vasopressors, sedation) are at the discretion of the clinical team. Co-enrollment in other studies will be permitted when that investigational product has little known hemodynamic effects and will be reviewed on a case-by-case basis.

#### Blinding

Intensivists, research personnel, ICU personnel, patients, members of the Executive and Steering Committees, and the data analysts will be blinded to the treatment allocations.

Only the pharmacist at the Research Pharmacy who is responsible for conducting the treatment allocation and preparing the study drug (i.e., midodrine or placebo) will not be blinded. In a situation needing unblinding, only the unblinded center research coordinator will have access to the treatment allocation in the Randomize.net system. Unblinding will only occur if there is deemed to be a significant safety event as per the site principal investigator.

In any case of unblinding, the data collection and follow-up schedule will be maintained.

#### Primary outcome measure

The primary outcome is:
The length of ICU stay as measured in hours. We will include both timing of discharge decision and actual departure from ICU.

#### Secondary outcome measures

The secondary patient-centered outcomes will include:
Total and post-ICU length of stay in hoursDuration of IV vasopressor support in hours60- and 90-day all-cause mortalityRates of ICU readmissionRate of re-initiation of IV vasopressors

The health economic outcomes will include:
ICU costsHospital costsTotal healthcare costsCost-effectivenessQuality-adjusted life years (QALYs)

#### Safety outcome measures

It is recognized that the patient population in the ICU will experience a number of aberrations in laboratory values, signs, and symptoms due to the severity of the underlying disease and the impact of standard treatments in the ICU. These will not necessarily constitute adverse events (AEs) or serious adverse events (SAEs) unless they are considered to be related to study treatment or in the local principal investigator’s clinical judgement are not recognized events consistent with the patient’s underlying critical illness and/or chronic diseases and expected clinical course. Adverse events that will be monitored for this study are listed in Table 2.

In Canada, reporting of SAEs will follow the five recommendations for rational reporting of SAEs in investigator-initiated critical care trials of drugs in common use [18].

In contrast, unexpected safety events that are serious (i.e., fatal, life threatening, prolonging hospital stay, resulting in persistent or significant disability or incapacity, or constituting an important medical event according to local principal investigator) and considered by the local principal investigator to be at least possibly related to the trial procedures will be reported to the coordinating center within 24 h of becoming aware of the event. The coordinating center will inform applicable regulatory agencies of serious safety events possibly related to the trial procedures within 15 days of receiving the report if the safety event was neither fatal nor life-threating, or within 7 days if it was fatal or life-threatening.

Within 7 days of informing the regulatory agency of a serious unexpected safety event, the coordinating center will submit to the regulatory agency a report including an assessment of the importance and implications of findings. This information will be updated with the patient’s final status.

### Recruitment and data collection

Potentially eligible patients will be referred to the research team by intensivists and other ICU staff. The research team will confirm eligibility and the site principal investigator and co-investigators will confirm whether the patient or SDM may be approached for consent. If that is the case, the research team will obtain consent from the patient or SDM or will enroll and obtain consent as per local REB recommendations under a deferred consent model. A minimum of 4 sites in Alberta and Canada will be invited to participate with each site required to enroll at least 4 patients per month.

Daily data will be collected from day 1 until ICU discharge or 30 days, whichever occurs first. Outcome data will also be collected at 60 and 90 days. All study outcomes will be documented on the electronic case report forms (eCRF) (Additional file 3).

#### Time points

Baseline data: patient demographics, etiology for hypotension, severity of illness, pre-existing comorbidities, and clinical frailty scaleDaily data until ICU discharge or 30 days (whichever comes first): protocol adherence, co-interventions (administration of mechanical ventilation, renal replacement therapy, vasopressors, corticosteroids, intravenous fluids, blood products, sedatives, antimicrobials)60- and 90-day data: death or persistent organ dysfunction (defined as dependency on mechanical ventilation, renal replacement, or ongoing IV vasopressor use)

### Study follow-up and cohort retention

Once a patient is enrolled in the trial, the clinical site will make every reasonable effort to follow the patient for the entire duration of the study period. To minimize loss to follow-up at 90 days, the patient’s medical records will be reviewed first. If the data is not available in the medical record the patient or substitute decision-maker will be contacted directly.

Patients may withdraw their participation in the LIBERATE trial at any time. If a patient wishes to withdraw their consent from the study, we will use the following strategies to minimize the impact on the validity of the trial, meanwhile respecting the patient’s right to withdraw. We will seek a better understanding of the patient’s wishes and offer the following alternatives to complete withdrawal, which would include no further study drug exposure, data deletion, and sample destruction:
Discontinue study drug but allow ongoing data collectionDiscontinue study drug and ongoing data collection but allow for initial data inclusion

Should any patients withdraw from the study, we will not seek patient replacement.

### Intention to treat and ineligible patients

We will adhere to the intention-to-treat principle and data from patients will be analyzed in the group to which they have been allocated irrespective of protocol adherence. Reasons for protocol deviations, should they arise, will be recorded. In the special case of patients mistakenly randomized, we will allow post-randomization exclusions if (1) the information about ineligibility was available at randomization, (2) two members of the Steering Committee agree that the patient was mistakenly randomized, (3) patients did not receive the intervention, and (4) patients remain blinded to their allocation. All of the above criteria must be present for patients to be excluded post-randomization [19].

Patient eligibility will be adjudicated when either a clinical site or the coordinating center suspects ineligibility. Two members of the Steering Committee will review all relevant information (i.e., hospital records) available at the time of randomization and adjudicate if the patient is eligible or ineligible. To be considered ineligible, the patient must have been ineligible at the time of randomization. If the adjudicators determine that the patient is eligible, the patient will remain in the trial. If they determine that the patient is ineligible, the patient will be withdrawn from the trial. Patients should not be withdrawn until confirmation is received from the coordinating center.

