### Statistical analyses

All patients will be analyzed as randomized in accordance with the intention-to-treat principle. However, we will also plan a secondary efficacy analysis including patients who received all study drug doses (per protocol analysis). The criterion for statistical significance will be based on alpha = 0.05. All tests will be two-sided, and all analysis will be performed using STATA v16 or later.

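### Two adjacent paragraphs give different rules for a patient found ineligible after receiving study drug

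*Protocol article*

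**What the plan says.** The section on intention to treat and ineligible patients opens with the principle that "data from patients will be analyzed in the group to which they have been allocated irrespective of protocol adherence". The Statistical analyses section repeats it: "All patients will be analyzed as randomized in accordance with the intention-to-treat principle".

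The first paragraph then makes one exception, for patients randomised by mistake. Two of its four criteria are "1) the information about ineligibility was available at randomization" and that two Steering Committee members agree on the mistake. The other two are "3) patients did not receive the intervention, and (4) patients remain blinded to their allocation". The paragraph closes the list firmly: "All of the above criteria must be present for patients to be excluded post-randomization".

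The second paragraph describes adjudication. It starts on suspicion: "Patient eligibility will be adjudicated when either a clinical site or the coordinating center suspects ineligibility". Two Steering Committee members look at what was available at randomisation, and the test is "To be considered ineligible, the patient must have been ineligible at the time of randomization". A patient judged eligible stays in the trial. For the opposite finding the text says: "If they determine that the patient is ineligible, the patient will be withdrawn from the trial". Sites must wait for the coordinating centre's confirmation before withdrawing anyone.

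**The concern.** The four-criterion rule protects intention to treat because it confines exclusions to patients who were ineligible on baseline facts and never took study drug. The adjudication paragraph ends in an outcome of its own that omits the dosing and blinding criteria. A site or coordinating centre holding a dosed, ineligible patient therefore has two instructions that cannot both be followed.

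This is unlikely to be a remote case. The Trial interventions section starts study drug at study inclusion, and nothing confines adjudication to the time before the first dose. Suspicion can easily come later, and that is where the rules diverge.

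Referral could also be related to outcome. One exclusion criterion is a judgement that death, or withdrawal of life-sustaining therapy, is expected within 24 hours. An early death invites people to revisit that judgement. It also shortens a stay counted simply in ICU hours, which is the primary outcome, and it counts in 60- and 90-day mortality. Which patients are put forward for review could therefore depend on events after dosing, even if the review itself looks only at baseline facts.

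**Working it through.** **Step 1. Set the two paragraphs side by side.**

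| Condition | Paragraph 1 (exclusion) | Paragraph 2 (withdrawal) |
|---|---|---|
| Ineligible on information available at randomisation | Required | Required |
| Two Steering Committee members agree | Required | Required |
| Patient did not receive the intervention | Required | Not mentioned |
| Patient still blinded | Required | Not mentioned |
| Force of the rule | Exclusion is allowed | Withdrawal is directed |

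Paragraph 2 covers the first two criteria and omits the other two.

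**Step 2. Apply both to one case.** Take a patient who was ineligible at randomisation on information then available, has received a dose, and is later adjudicated ineligible. Under paragraph 1 the third criterion fails, so the patient may not be excluded. Under paragraph 2 the patient is to be withdrawn. For an undosed patient who is still blinded the two paragraphs are compatible, so the conflict centres on dosed patients, with the same gap for any patient who has been unblinded.

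**Step 3. Check the planned numbers.** The Sample size section gives 161 per arm and an 8% allowance for loss to follow-up: 161 / (1 − 0.08) = 175.0 per arm, or 350 in total. This reproduces the stated figure. The base of 161 cannot be checked, because the article gives no mean or standard deviation.

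**Step 4. Gauge the effect on power, for scale only.** Assume the usual two-sided comparison of two means with alpha 0.05 and 80% power, n = 2 (1.960 + 0.842)² (SD/Δ)², and solve for the spread:

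- SD/Δ = √(161/2) / 2.802 = 8.972 / 2.802 = 3.20.
- With Δ equal to 20% of the mean, SD/mean = 0.20 × 3.20 = 0.64. This is implied by the calculation, not stated in the article.

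Power is then Φ(√(n/2) / 3.20 − 1.960). The article gives no removal rate, so the rates below are assumptions. They apply to the 161 per arm left after the 8% loss.

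| Assumed further removal | n per arm | Power |
|---|---|---|
| 0% | 161.0 | 80.0% |
| 2% | 157.8 | 79.2% |
| 5% | 152.9 | 78.0% |
| 10% | 144.9 | 75.7% |

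The loss of power is small across the range. What matters is who is removed and when.

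**The case against.** The best defence is that paragraph 2 is only the procedure for the Steering Committee criterion. It names the same two-member review and the same evidence, and the closing sentence of paragraph 1 can be read as still governing exclusion. That reading is reasonable and may be what was intended. The text does not say it, though: paragraph 2 ends in an unconditional result and does not refer back to the four criteria.

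The safeguards also count. Adjudicators see only what was known at randomisation, sites and Steering Committee are blinded, and withdrawal waits for central confirmation. Removal that differs by arm is therefore much less likely than it would be in an open review. This stands, with the limit that the safeguards govern how a case is judged and not which cases are referred.

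Three stronger readings are tempting, and the article does not support them:

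- **A reader might infer that intention to treat is broken.** Being withdrawn from the trial is not defined as removal from the analysis set, and the Statistical analyses section still promises analysis of all patients as randomised. The departure follows only if withdrawal is taken in that sense.
- **A reader might infer that safety and mortality data are lost.** Data deletion is mentioned only in the follow-up section, for complete withdrawal of consent, and that section offers lesser forms. Carrying it over to adjudicated ineligibility is inference.
- **A reader might take the third criterion to mean midodrine only, which would exempt every placebo patient.** Table 2 lists midodrine or placebo together under Intervention, and blinded adjudicators could not apply a midodrine-only test.

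A full protocol or analysis plan might settle the matter. The point here is not an omission, however: the published text states two rules that diverge.

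**Conclusion.** The point holds as an inconsistency in a stated rule. For a dosed patient later adjudicated ineligible, the first paragraph bars exclusion and the second directs withdrawal. Whether this harms the analysis rests on two conditions: that the second paragraph is applied literally, and that withdrawal means leaving follow-up or analysis. If both hold, treated patients could be removed from the as-randomised population after their course has begun.

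The number affected cannot be estimated from the article. Any assumed rate of late-found ineligibility would also have to separate dosed patients, who are in dispute, from undosed ones, whom the first paragraph may properly exclude. The 8% allowance is for loss to follow-up and was not set for such removals. The power effect is minor on the assumptions shown. The matter should be corrected because leaving it open lets the primary analysis population depend on a choice made after randomisation, and the correction is cheap.

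**What to change.** Reconcile the two paragraphs with two sentences:

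1. Make the withdrawal sentence subject to the first paragraph, for example: *A patient adjudicated ineligible is withdrawn only if all four criteria above are met.*
2. State what happens otherwise, for example: *A patient adjudicated ineligible who has received any study drug remains in follow-up and in the intention-to-treat and safety analyses.*

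Whether study drug continues in such a patient is a separate clinical matter, on which no position is taken here.

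The cost is a short protocol clarification. It needs no new data, no change to the sample size and no change to the adjudication process. It should be made without reference to outcomes by arm, and before the database is locked.
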